## Abstract

Background: With an aging population, developing non-pharmacological interventions (NPIs) to delay dementia has become critical. Apart from cognitive decline, dementia is associated with multiple pathophysiology, including increased oxidative stress, dysregulated gene expressions, cytokine, neurotrophin, and stress markers, telomere shortening, and deteriorations in brain connectivity. Although mindfulness practices have been proposed to ameliorate these biological changes, no empirical studies were conducted. We thus aimed to investigate the effects of mindfulness awareness practice (MAP) to prevent cognitive decline and improve peripheral biomarkers in community-dwelling older adults diagnosed with mild cognitive impairment (MCI). Methods/Design: This was a single-blinded and parallel-group randomized controlled trial with two arms (intervention and active control arms), conducted over nine months. A total of 60 consenting community-dwelling older adults diagnosed with MCI were planned to be randomized in a 1:1 ratio to either the MAP or the Health Education Program (HEP). Interventions were performed weekly for the initial 12 weeks, and monthly for the subsequent six months. Outcome measures were assessed at baseline, 3-month, and 9-month post-intervention by blinded assessors. Primary outcomes were neurocognitive tests, comprehensive peripheral biomarkers, and brain imaging scans. Secondary outcomes included basic health screening measures, affective symptoms, and measures of physical functions. Linear-mixed models were used to examine the effects of MAP on these outcome measures. Significance: This is the first randomized controlled trial to systematically investigate the effects of a mindfulness intervention in improving cognitive functions and various biomarkers in community-dwelling older adults diagnosed with MCI. Our findings have the potential to inform mindfulness intervention as a novel approach to delay dementia.

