### 3.10. Statistical Analysis

Based on previous studies [35,49,50,51] examining the effects of mindfulness on the means and SDs for co-primary outcomes chosen for this study, i.e., fluid biomarkers and neurocognitive tests, we estimated the effect sizes to be 0.5. Hence, we required 24 participants in each group to have a power of 80% to detect statistical significance at 5% level. Considering a potential 20% drop-out rate, 30 participants needed to be assigned to each group at baseline. Hence, the targeted total sample size was 60.

All demographic and outcome measures were expressed as mean ± standard deviation (SD). We used either Fisher’s exact, Student’s or chi-square *t*-test to examine the differences in the baseline variables, as per the nature of the data. In the event the raw values of the measures were not conforming to the normality assumption, the raw values were natural log-transformed for subsequent analyses. Successful normalizations were based on dot plots, skewness, and kurtosis.

We employed the linear-mixed model to examine the treatment effects of MAP on the biomarkers and psychometric scale outcome measures, compared to the active control group, HEP, over the three time-points. For the psychometric and fluid biomarker measures, we performed intention-to-treat analyses using linear-mixed model, because it is robust to missing data. The model considers all the participants included in the baseline, regardless of whether they have missing values at subsequent follow-ups [52]. For the neuroimaging measures, since the drop-out rates were much higher, we used per-protocol analyses, where only participants that completed the intervention and had neurocognitive and neuroimaging scans at follow-ups were included in the ANOVA analyses.

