In each of the linear-mixed models, we entered the outcome measure of interest as the dependent variable. The time-points of the intervention, treatment arm, and an interaction term between time-points and treatment arm were treated as the independent variables. Covariates for all the models included the baseline values of the respective outcome variable, age, sex, and years of formal education. We also collected measures for other covariates relevant to MCI and dementia, including the geriatric depression scale (GDS) and geriatric anxiety inventory (GAI) clinical cut-offs, history of cardiovascular diseases, and history of myocardial infarction. These additional covariates were explored to examine their effects on the basic models, using the model fit statistics, namely the Akaike information criterion (AIC) and Bayesian information criterion (BIC) values. In the final models, for the additional covariates, only the significant ones for each model were retained. We based all the analyses on the intention-to-treat principle, hence all the participants who had measures at at least one time-point were included in the analysis. All statistical analyses were and will be further performed using the Statistical Package for the Social Sciences (SPSS) Statistics for Windows, version 23.0 (IBM Corp., Armonk, NY, USA). A two-tailed *p*-value of < 0.05 was and will be considered statistically significant.

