### 4.3. Maintenance: Adherence Rate and Lost to Follow-Up for Primary and Secondary Outcome Measures

Adherence or attendance rates were approximately 88 and 89% for the MAP and HEP groups, respectively. Since we did not require all the participants to consent to bio-specimen collection and neuroimaging scans, there could be differences in lost to follow-ups. Lost to follow-ups for fluid biomarker, psychometric and neuroimaging measures are presented in Figure 4.

For the fluid biomarker measures, the total number of lost to follow-up cases at 9-month time-point was 9 in the MAP (32.14%) and 6 (22.22%) in the HEP group. For the psychometric measures, similar lost to follow-up rates at 9-month time-point were observed: 10 in the MAP (35.71%) and 8 in the HEP group (29.63%). For the neuroimaging measures, there were 18 lost to follow up cases in the MAP (64.29%) and 21 lost to follow up cases in the HEP group (77.78%).

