This RCT thus filled the gap in the literature for a robust and rigorously conducted RCT with the inclusion of an active control group to determine the effectiveness of a mindfulness intervention with older adults clinically diagnosed with MCI [51]. In particular, this study contributes to addressing the scarcity in the literature on mindfulness intervention focusing on an array of multiple cognitive abilities and diverse peripheral biomarkers in older adults with MCI, utilizing parallel-group RCT design, which is conducted with an Asian population. The neurocognitive tests, measures on affective symptoms and physical limitations, neuroimaging scans, a comprehensive set of peripheral biomarkers encompassing blood, saliva, fecal, and urine biomarkers provided pilot evidence of the biological effects and thus illuminated the biological underpinnings of mindfulness intervention with older adults diagnosed with MCI. This RCT is, to date, the largest RCT on mindfulness intervention with older adults clinically diagnosed with MCI. Furthermore, this study did not only study the short-term effects, but also the long-term effects of mindfulness intervention, making this study one of the longest interventional trials employing mindfulness as a novel approach to delay cognitive impairments and studying its long-term cognitive and biological effects systematically.

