## 6. Conclusions

In investigating the multi-faceted biopsychological outcomes of MCI, this study presented pilot data on whether mindfulness intervention improved cognition and several well-established pathophysiology of MCI and dementia. As we have shown, the effectiveness of a mindfulness intervention with MCI with the use of an active control group, future studies could add an additional wait-list control group to further evaluate the efficacy of the intervention. Apart from showing pilot data on MCI as an intermediate disease stage that is amenable to mindfulness psychologically, positive findings on the biomarkers also opened the possibility that MCI represents a stage of disease with malleable biology. Hence, this RCT presented actionable targets, which are modifiable risk factors of dementia, in response to a novel mindfulness intervention. The results from this RCT could inform policymakers of the need to support low-cost and self-directed psycho-social programs and activities to prevent dementia and even reverse cognitive decline in MCI. Indeed, this RCT, together with the other RCTs involving cognitive stimulating activities we have previously conducted [43,64,65,66,67], provided pilot scientific evidence for the nationwide rollout of the dementia prevention program, termed the Aging-Well-Everyday (AWE) program, in Singapore. Backed by robust scientific evidence, this is a first-of-its-kind community-based multimodal intervention performed by fostering close collaboration among governmental organizations, non-governmental organizations, and academic institutions, enabling a truly community-integrated model. For sustainability of the AWE program, we work closely with community centers in eight housing estates, and these centers are partly funded by the People’s Association which has financial support from the government. With our online program in the Malay language, we hope to extend to neighboring countries, such as Indonesia and Malaysia. We envision that this could be the model for future studies on novel NPIs to examine real-world intervention effects, to extend the interventions’ benefits to the community and potentially halt the increased incidence of dementia. With mindfulness intervention as a health promotion and secondary preventive strategy, older adults could age in place in the community.

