**Figure 4 ijerph-18-10205-f004:**
[figure not shown]
CONSORT 2010 Flow diagram for co-primary outcome measures.

**Table 1 ijerph-18-10205-t001:** A summary of assessments or measures collected throughout the three time-points.

Assessments or Measures	Baseline	At 3-Month	At 9-Month
Social-demographic Questionnaire	√	-	-
Basic Health Screening	√	√	√
Physical Assessments (ADL and IADL)	√	√	√
Mini Mental State Examination (MMSE)	√	√	√
Depression and Anxiety Screening Tests (GDS and GAI)	√	√	√
Clinical Dementia Rating (CDR) Scale	√	√	√
Neurocognitive Tests	√	√	√
MRI Brain Scan	√	√	-
Blood Sample	13 mL	8 mL	13 mL
Urine Sample	15 mL	-	15 mL
Fecal Sample	√	√	√
Saliva Sample	√	√	√

ADL = Activities of Daily Living; IADL = Instrumental Activities of Daily Living; MMSE = Mini-Mental State Examination; GDS = Geriatric Depression Scale; GAI = Geriatric Anxiety Inventory; CDR = clinical dementia rating; MRI = Magnetic Resonance Imaging.

**Table 2 ijerph-18-10205-t002:** Comparisons of the baseline demographic and characteristics between participants in the Mindful Awareness Practice (MAP) and Health Education Program (HEP) Arms (N = 55).

Baseline Demographics and Characteristics	MAP, Treatment; n (%) or Mean (SE) (n = 28)	HEP, Control; n (%) or Mean (SE) (n = 27)	*p*-Value
Age (in years)	71.89 (1.14)	70.67 (1.19)	0.46
Sex			
Male	8 (28.60%)	6 (22.20%)	0.59
Female	20 (71.40%)	21 (77.80%)	
MCI subtypes			
aMCI	13 (46.40%)	8 (29.6%)	0.27
Non-aMCI	15 (53.6%)	19 (70.4%)	
Years of Formal Education	5.27 (5.02)	3.44 (4.27)	0.16
Ethnicity			
Chinese	27 (96.40%)	27 (100%)	1.00
Indian	1 (3.60%)	0 (0%)	
Others	0 (0%)	0 (0%)	
Employment Status			
Retired	14 (51.90%)	11 (40.70%)	0.14
Full-time worker	0 (0%)	0 (0%)	
Part-time worker	0 (0%)	4 (14.80%)	
Housewife	13 (48.10%)	12 (44.40%)	
Marital Status			
Single	1 (3.70%)	0 (0%)	0.29
Married	18 (66.70%)	14 (51.90%)	
Divorced	2 (7.40%)	1 (3.70%)	
Widowed	6 (22.20%)	12 (44.40%)	
MMSE (Total Scores)	24.59 (0.63)	24.70 (0.75)	0.91
GDS			
<5	18 (64.30%)	22 (81.50%)	0.15
≥5	10 (35.70%)	5 (18.50%)	
Attendance rate (%)	88.6 (12.48)	87.0 (19.11)	0.77
Total number of metabolic disorders	1.44 (0.22)	1.52 (0.16)	0.79
Presence of diabetes	6 (22.2%)	8 (29.6%)	0.76
BMI, kg/m^2^	24.76 (0.85)	24.06 (0.67)	0.53
Total number of chronic diseases	2.04 (0.33)	2.85 (0.25)	0.66
Total number of medications taken	2.89 (0.44)	2.96 (0.39)	0.90
Total number of participants taking psychotropic medications	1 (3.70%)	0 (0%)	1.00

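### The primary outcomes are defined in two ways, and one unadjusted p<0.05 rule applied across whole outcome classes holds 5% per test, not for a claim on the primary set

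*Protocol article*

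**What the plan says.** The protocol article describes the primary outcomes in three places, and they do not agree.

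- **Abstract:** "Primary outcomes were neurocognitive tests, comprehensive peripheral biomarkers, and brain imaging scans". That is three classes, including imaging.
- **Section 3.10, sample size paragraph:** "co-primary outcomes chosen for this study, i.e., fluid biomarkers and neurocognitive tests". That is a closed list of two classes, without imaging.
- **Figure 4 and section 4.3:** the caption reads "CONSORT 2010 Flow diagram for co-primary outcome measures", and section 4.3 says "Lost to follow-ups for fluid biomarker, psychometric and neuroimaging measures are presented in Figure 4". Imaging is again under the co-primary label.

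No individual test, marker, scan measure or visit is singled out as decisive. The Discussion describes the biomarker class as "a comprehensive set of peripheral biomarkers encompassing blood, saliva, fecal, and urine biomarkers".

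On testing, section 3.10 enters each outcome measure as the dependent variable of its own linear mixed model, with time, arm and their interaction. Imaging goes to a per-protocol ANOVA. The section closes with one rule for all analyses: a two-tailed p-value below 0.05 "was and will be considered statistically significant". The sample size is a single calculation at the 5% level with 80% power.

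**The concern.** When whole classes of measures are primary and each measure is judged alone at 0.05, the chance that at least one primary result is falsely positive exceeds 5%, and it grows with the number of measures. The article does not say which results, or how many, would make the trial positive.

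The article does read outcomes one by one. The limitations paragraph of the Discussion attributes missing significance on several measures to reduced power. The Conclusions say that "positive findings on the biomarkers also opened the possibility that MCI represents a stage of disease with malleable biology", state that effectiveness has been shown, and offer the results to policymakers and as support for a national programme. Readers would take those statements as resting on a 5% error rate.

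The disagreement over imaging has its own consequence. Section 4.3 reports imaging losses of 64.29% and 77.78% in the two arms, and imaging has a different analysis population and method from the other classes. Whether a primary outcome is analysed in that way depends on which part of the article is read.

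**Working it through.** **1. Inputs.**
- Per-test level: two-sided 0.05 (section 3.10).
- Number of classes: two (section 3.10) or three (Abstract; Figure 4 with section 4.3).
- Number of primary measures, k: not stated, so assumed.
- Correlation between tests: not stated, so 0, 0.3 and 0.5 are shown.

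**2. The plan's own level.** With one primary test (k=1), 1 − 0.95¹ = 5%. The stated level is right for a single test.

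**3. Several tests, each at 0.05.** If independent, the chance of at least one false positive is 1 − 0.95^k:
- k=2: 1 − 0.9025 = 9.8%
- k=3: 1 − 0.8574 = 14.3%
- k=20: 1 − 0.3585 = 64.2%

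For correlated tests, equicorrelated standard normal statistics were simulated (200,000 draws), counting draws in which any |Z| exceeded 1.96.

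| k (assumed) | independent | correlation 0.3 | correlation 0.5 |
|---|---|---|---|
| 2 (one per class, section 3.10) | 9.8% | 9.5% | 9.1% |
| 3 (one per class, Abstract) | 14.3% | 13.6% | 12.5% |
| 5 | 22.6% | 20.7% | 18.4% |
| 10 | 40.1% | 35.2% | 28.7% |
| 20 | 64.2% | 54.1% | 41.8% |

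The lowest count that either definition allows already exceeds 5% at every correlation shown.

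**4. Visits.** Table 1 shows MRI at baseline and 3 months only, and urine at baseline and 9 months only. The mixed models carry one time-by-arm interaction term. One test per measure is therefore the fair count, and k should not be doubled for two follow-ups.

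**5. The all-must-succeed reading.** Under a strict co-primary rule, in which every outcome must be significant, type I error would not be inflated and power would fall instead. The article states no such rule. No joint power is derived here from the stated 80%, because that figure does not reproduce for a plain two-group comparison. With 24 per group, a standardised effect of 0.5 and two-sided 5%, power is about 41% (40% by t-test). A baseline-adjusted analysis would need about 23 per group if the baseline correlation were 0.8, but no correlation is given. That is a separate matter.

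**The case against.** The strongest case on the other side has four parts.

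- **This is a condensed article.** An itemised outcome list and a multiplicity procedure often sit in the full protocol or analysis plan, which is not shown. That stands as far as their absence goes. It does not cover what the article itself fixes: two incompatible primary definitions and one unqualified threshold.
- **The 5% and 80% can be read as per-outcome figures.** This is fair. The article makes no explicit family-wise claim, so a reader should not infer that the two figures contradict each other. The difficulty comes when per-outcome results become a general statement of effectiveness.
- **The trial is called proof-of-concept (Discussion) and its data pilot data (Conclusions).** This softens the consequence. It would justify unadjusted testing if the outcomes were labelled exploratory, but they are labelled primary, and the Conclusions go on to effectiveness and policy.
- **The scale is unknown.** This also stands. A reader might infer dozens of primary tests from the biological processes in the Abstract and Introduction. Those passages describe the pathophysiology of dementia and are not an outcome list, so a large k remains an assumption. Independence also gives the highest of the figures shown.

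Two other tempting inferences fail. The disagreement over imaging does not itself inflate error; it leaves the primary set undefined. And the Conclusions do not explain away negative results; the remark on low power is in the limitations paragraph of the Discussion.

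**Conclusion.** The point holds in a bounded form. The Abstract, and Figure 4 read with section 4.3, conflict with section 3.10 on whether imaging is primary. The stated 0.05 rule controls error for each test only. The chance of at least one false positive among the primary outcomes is at least about 9% to 14%, taking one measure per class and correlations from 0 to 0.5. With an assumed 20 measures it would be roughly 42% to 64%. These figures assume equal correlations, one test per measure and no true effect on any measure. They do not show that any reported result is false, and the documents do not support a single figure for the inflation.

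The issue should be settled before the remaining analyses are reported, because it decides what counts as a positive trial.

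**What to change.** 1. Reconcile the Abstract, section 3.10, section 4.3 and the Figure 4 caption into one list of primary outcomes that says whether imaging belongs to it.
2. Keep a single primary outcome and visit only if these were fixed before the data were seen. The Trial Status section says part of the results are already published, so neither should be chosen now.
3. Otherwise, if a 5% claim is made for the declared set, report p-values adjusted with one stated procedure across the whole set, for example Holm. Use one test of the time-by-arm effect per measure, over the visits collected in Table 1: imaging has only the 3-month follow-up and urine only the 9-month one.
4. If no such claim is made, say that 0.05 applies per outcome and that the results are exploratory, in line with the proof-of-concept label in the Discussion.
5. Apply this to the remaining analyses. Limit the effectiveness and policy statements in the Conclusions to what survives adjustment, or label them hypothesis-generating.

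The cost is a little extra analysis and rewording, and fewer nominally significant results. Under Holm the smallest p-value must fall below 0.05/k: 0.025 for k=2, 0.0167 for k=3 and 0.0025 for an assumed k=20.

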## 1. Introduction

With an accelerated demographic shift towards increased population aging, the incidence of dementia has been forecasted to escalate. In 2010, 35.6 million people were estimated to be diagnosed with dementia. It is postulated that this number will double every 20 years, culminating in 115.4 million cases in 2050 [1]. This issue has multi-faceted implications, including increasing burdens of affected patients, family members, caregivers, healthcare systems, and the economy. Dementia is, therefore, one of the most urgent public health issues globally. However, despite intensified efforts and numerous attempts in pharmaceutical trials, all new candidates for pharmacological intervention have failed in the past decade [2], except for one recent U.S. Food and Drug Administration (FDA)-approved drug. Furthermore, the existing treatments for dementia have limited efficacy and are only effective for a few months [3]. Hence, validating the potentials of preventive non-pharmaceutical interventions (NPIs) to slow and even reverse cognitive decline has received substantial attention in recent years, particularly at the preclinical dementia stage. Notably, if the onset and the progression of dementia could be delayed by just one year through any forms of interventions, there will be approximately 9.2 million fewer cases of dementia in 2050 [4], equaling an 8% decrease in the total projected dementia cases.

MCI is a transitional state between normal aging and very early dementia [5,6,7]. Individuals with MCI have an increased risk of dementia; although a small percentage of patients will revert to be cognitively healthy, 50% of MCI cases progress to develop AD [7]. Early identification, coupled with early preventive intervention at the MCI stage, could thus potentially slow and/or reverse cognitive decline. One way for such secondary prevention is through improving MCI- or dementia-associated modifiable risk factors [8]. Additionally, it has been previously shown that older adults with MCI are still cognitively able to learn and acquire new techniques [9]. With the pathology not as extensive as dementia, MCI could also potentially represent a period of malleable pathophysiology.

Given this immense potential, the search for non-pharmacological interventions (NPIs) to enhance cognition and to delay or even reverse cognitive decline has accelerated in the past decade. Amongst many different types of interventions, there have been increasing interests on the potential positive effects of mindfulness intervention on cognition. Mindfulness is defined as “paying attention in an intentional and non-judgmental way to the present moment” [10]. It has been shown to be a cost-effective, acceptable, and non-invasive approach to ameliorate the symptoms of a broad spectrum of disorders. Specifically, mindfulness interventions have demonstrated positive effects on various psychiatric disorders [11], including depression, social anxiety, obsessive-compulsive disorder, bipolar disorder, attention deficit disorder, and addiction. This raises the question of whether mindfulness interventions are applicable for older adults, who have comparatively short attention spans and a lifetime accumulation of allostatic stress [12]. Systematic reviews [13,14] concluded that meditation interventions, a closely related NPI, for older adults are feasible, with ample preliminary evidence suggesting that meditation may delay cognitive decline. However, most evidence was gleaned from epidemiological studies [15,16], many of which were of cross-sectional design, impeding causal inferences. Furthermore, the effectiveness of mindfulness intervention in older adults diagnosed with MCI is unknown.

Several theoretical propositions on how mindfulness could improve cognition have been postulated. Lutz et al. (2008) and McVay et al. (2009) proposed that by progressing through the two stages of mindfulness practices, namely focused attention and subsequently open monitoring, older adults’ attention and working memory could be improved [17,18]. Apart from attention and memory, executive function was also theorized to improve with mindfulness practice [19]. However, many prospective mindfulness interventional trials with non-MCI populations have shown conflicting results. To our best knowledge, only two small RCTs on mindfulness intervention with older adults diagnosed with MCI have been conducted, both with a small sample size of 14 participants each, and reported conflicting results in various cognitive measures [20,21]. This small sample size presents significant issues in achieving adequate statistical power, which could be one of the many reasons for the non-significant findings, instead of a lack of intervention effects [22]. Furthermore, a limited panel of outcome measures were collected in previous mindfulness RCTs with MCI, as they focused solely on cognitive outcomes and, to a smaller extent, neuroimaging measures [20,21]. Hence, there is a severe scarcity of evidence gathered from peripheral biomarker data.

The sole reliance on self-reported measures for assessing improvements upon undergoing mindfulness intervention has been identified as a major limitation [23,24,25,26]. This limitation calls for the need for biomarker examinations for mindfulness intervention [27]. As the pathophysiology of MCI and dementia is multi-faceted, they include the deterioration in neuronal functional connectivity, increased oxidative stress [28], increased low-grade systemic inflammation [29,30,31] and stress [32,33], decreased neurotropic factors [34], dysregulated gene expression [35], and shortening of telomere length [36]. However, no studies have yet to examine the effect of a mindfulness intervention on peripheral biomarkers in older adults clinically diagnosed with MCI. Hence, whether mindfulness intervention could significantly improve multiple biomarkers associated with MCI and dementia pathophysiology remains unknown. 

Several other significant methodological limitations could also be responsible for the mixed findings on the effects of mindfulness interventions. Amongst them, apart from limited causal inferences, epidemiological study design could also risk residual confounding. Even with the RCT design, some mindfulness interventions employed a single-group design and thus lacked a control group, which raises the possibility of bias and confounding. The 8-week intervention duration, which is typical of mindfulness interventions [37], raises questions on the long-term effects and the sustainability of the intervention. To the best of our knowledge, only one mindfulness trial has an extended follow-up period of up to 18 months, although the sample was not older adults diagnosed with MCI [38]. Furthermore, due to the inherent genetic and lifestyle differences, the effects of mindfulness intervention among Asian populations have remained mostly unexplored [39]. Conversely, we have previously demonstrated that mindfulness practice was acceptable to Singaporean Chinese and did not carry the stigma of mental illness [39], substantiating the rationales to perform such an intervention with Singaporeans. Because of these issues and motivations, a RCT on mindfulness intervention that addresses these limitations was advocated [40]. In this paper, we detail the protocol and implementation outcomes of this RCT. 

